# The impact of the HEART risk score in the early assessment of patients with acute chest pain: design of a stepped wedge, cluster randomised trial

**DOI:** 10.1186/1471-2261-13-77

**Published:** 2013-09-26

**Keywords:** HEART score, Chest pain, Clinical prediction rule, Risk score implementation, Impact, Stepped wedge design, Cluster randomised trial

## Abstract

**Background:**

Chest pain remains a diagnostic challenge: physicians do not want to miss an acute coronary syndrome (ACS), but, they also wish to avoid unnecessary additional diagnostic procedures. In approximately 75% of the patients presenting with chest pain at the emergency department (ED) there is no underlying cardiac cause. Therefore, diagnostic strategies focus on identifying patients in whom an ACS can be safely ruled out based on findings from history, physical examination and early cardiac marker measurement. The HEART score, a clinical prediction rule, was developed to provide the clinician with a simple, early and reliable predictor of cardiac risk. We set out to quantify the impact of the use of the HEART score in daily practice on patient outcomes and costs.

**Methods/Design:**

We designed a prospective, multi-centre, stepped wedge, cluster randomised trial. Our aim is to include a total of 6600 unselected chest pain patients presenting at the ED in 10 Dutch hospitals during an 11-month period. All clusters (i.e. hospitals) start with a period of ‘usual care’ and are randomised in their timing when to switch to ‘intervention care’. The latter involves the calculation of the HEART score in each patient to guide clinical decision; notably reassurance and discharge of patients with low scores and intensive monitoring and early intervention in patients with high HEART scores. Primary outcome is occurrence of major adverse cardiac events (MACE), including acute myocardial infarction, revascularisation or death within 6 weeks after presentation. Secondary outcomes include occurrence of MACE in low-risk patients, quality of life, use of health care resources and costs.

**Discussion:**

Stepped wedge designs are increasingly used to evaluate the real-life effectiveness of non-pharmacological interventions because of the following potential advantages: (a) each hospital has both a usual care and an intervention period, therefore, outcomes can be compared within and across hospitals; (b) each hospital will have an intervention period which enhances participation in case of a promising intervention; (c) all hospitals generate data about potential implementation problems. This large impact trial will generate evidence whether the anticipated benefits (in terms of safety and cost-effectiveness) of using the HEART score will indeed be achieved in real-life clinical practice.

**Trial registration:**

ClinicalTrials.gov 80-82310-97-12154.

## Background

Patients presenting with chest pain at the emergency department (ED) pose a diagnostic challenge. Chest pain can be a symptom of an acute coronary syndrome (ACS), i.e. acute myocardial infarction (AMI) or unstable angina, which is the case in approximately 20% of the patients and requires prompt treatment. In the remaining 80%, chest pain is caused by many other, usually not life-threatening, conditions [1]. Unfortunately, decision-making in chest pain patients is hampered by limited predictive power of patient characteristics, including signs, symptoms and additional tests [1-3]. Therefore, physicians face the challenge of not wanting to miss an ACS on the one hand, while avoiding too many unnecessary diagnostic procedures that can be time-consuming and patient burdening on the other hand. Currently, the fear of missing a relevant cardiac condition makes physicians cautious and, to be on the safe side, a large proportion of patients are kept in the hospital from several hours to days for monitoring or additional testing.

Diagnostic strategies in patients with chest pain therefore focus on identifying patients in whom ACS can be safely ruled out based on readily available clinical findings from history, physical examination and early marker measurement of cardiac damage. Recent guidelines suggest the use of well-developed and validated risk scores to stratify patients in the emergency room [4-6]. Several prognostic risk scores have been developed for patients diagnosed *with ACS*, such as the TIMI (Thrombolysis in Myocardial Infarction) risk score and the GRACE (Global Registry of Acute Cardiac Events) risk score [7-9]. However, scores that *identify ACS* in patients suspected of ACS in the emergency setting and predict short-term mortality or coronary intervention are not available. The HEART score has been specifically developed for risk stratification in all patients with chest pain presenting at the ED.

The HEART score incorporates all five important elements of clinical judgement in chest pain patients: History, ECG (electrocardiogram), Age, Risk factors and Troponin (see Table 1). Similar to the Apgar score, applied worldwide to assess the need for intensive care in new-borns [10], each of the five elements is appreciated with 0, 1 or 2 points. The sum of all five elements results in a score between 0–10, which can easily be calculated.

**Table 1 T1:** Elements to calculate HEART score for chest pain patients at the emergency department

**History**	Highly suspicious	2
	Moderately suspicious	1
	Slightly or non-suspicious	0
**ECG**	Significant ST-depression	2
	Nonspecific repolarization disturbance	1
	Normal	0
**Age**	≥ 65 years	2
	>45 – <65 years	1
	≤ 45 years	0
**Risk factors**	≥ 3 risk factors*, *or* history of atherosclerotic disease^	2
	1 or 2 risk factors	1
	No risk factors known	0
**Troponin**	≥ 3x normal limit	2
	>1 - <3x normal limit	1
	≤ normal limit	0
**Total**		
**Range: 0-10**		

*Risk factors include: currently treated diabetes mellitus, current or recent smoker, diagnosed and/or treated hypertension, diagnosed hypercholesterolemia, family history of coronary artery disease (CAD) , obesity (body mass index (BMI) >30).

^History of atherosclerotic disease include: coronary revascularization, myocardial infarction, stroke, or peripheral arterial disease, irrespective of the risk factors for CAD.

The HEART score has been externally validated in various patient populations with a total of 6174 patients and its predictive effectiveness has been demonstrated [11-14]. Table 2 depicts an overview of these validation studies. In the Dutch multicenter validation study, major adverse cardiac events (MACE) occurred in 1.7% (95% CI 1.18-2.22) of all patients with a HEART score of 3 or lower. This is comparable with the around 2% incidence of ACS among discharged chest pain patients reported in the literature [15,16]. Importantly, none of the patients in the low-risk HEART category experienced unexpected sudden cardiac death in our validation studies. MACE occurred in 16.6% of all patients with intermediate HEART scores (4–6), and in 50.1% of all patients with high HEART scores (7–10). Similar results were observed in relevant patient subgroups, such as women, elderly or diabetics [12]. Notwithstanding these promising validation results, the impact of the use of the HEART score in daily clinical practice remains to be established. The HEART score provides the physician with a formal risk score and a recommendation whether a chest pain patient should be admitted or not. A safe and early discharge could potentially result in a significant reduction of patient burden, hospital admissions and health care costs.

**Table 2 T2:** Summary of results of previous validation studies of the HEART score

				**Total**
**Number of patients**	N = 880 [12]	N = 2388 [13]	N = 2906 [14]	N = 6174
**Design**	Retrospective	Prospective	Prospective	
**Countries**	The Netherlands	The Netherlands	9 countries in the Asia-Pacific region	
**Participating hospitals**	4	10	14	
**Inclusion period**	Jan ‘06 – Mar ‘06	Oct ‘08 –Nov ‘09	Nov ‘07 – Dec ‘10	
**Type of patients**	Patients presenting with chest pain at the ED	Patients presenting with chest pain at the ED	Patients presenting with chest pain at the ED	
**MACE definition**	AMI, revascularisation, all cause death	AMI, revascularisation, stenosis managed conservatively, all cause death	AMI, revascularisation, death unless clearly non-cardiac	
**Duration of follow-up**	6 weeks	6 weeks	4 weeks	
**Cumulative incidence of MACE stratified by HEART scores**				
**0-3**	0.99%	1.7%	1.7%	1.6% (95%-CI 1.05-2.15)
**4-6**	11.6%	16.6%	14.3%	12.5% (95%-CI 11.34-13.66)
**7-10**	65.2%	50.1%	50.0%	49.4% (95%-CI 46.37- 52.43)

ED: emergency department.

AMI: acute myocardial infarction.

MACE: major adverse cardiac event.

95%-CI: 95%- confidence intervals.

Therefore, we designed the HEART Impact study to investigate whether the use of the HEART score in the management of chest pain patients indeed leads to these positive health effects, while not causing an increase in the occurrence of MACE.

## Methods/Design

### Study design: stepped wedge randomised trial

We will use a prospective, stepped wedge cluster randomised trial [17,18]. Our aim is to include 6600 unselected chest pain patients from 10 hospitals in the Netherlands during an 11-month period. Key study design features are shown in Figures 1 and 2. In a stepped wedge design, there is no randomisation at patient level, but hospitals will be randomised with respect to the timing at which they introduce the HEART score. See Figure 1. During the first month, all chest pain patients presenting to the ten hospitals will receive usual care. Then, during a 10-month period, each month one randomly allocated hospital will start to apply the HEART score (HEART period) and continue to do so until the end of the study. During the last month of the inclusion period all 10 hospitals will be using the HEART score.

**Figure 1 F1:**
[figure not shown]
The Stepped Wedge Design for the HEART Impact study.

**Figure 2 F2:**
[figure not shown]
**Flow of study and data collection in usual care period and in HEART period.** ED: emergency department. QoL:quality of life. EQ-5D: EuroQol Five-Dimensional. SF-36: short-form 36. iPCQ: productivity cost questionnaire. MACE: major adverse cardiac events.

### ‘Usual care’ and ‘HEART’ period

Usual care is defined as ‘daily practice of the cardiologist or attending emergency doctor to diagnose a patient with chest pain’. In this period, attending doctors assess the risk based on their clinical skills, previous experiences, gut feeling and various other criteria (for example, described in European Society of Cardiology Guidelines [6]), without using the HEART score. No attempt was made to explicitly standardise usual care across all hospitals. The assessment will typically include: gender, age, medical (cardiac) history, symptoms, risk factors, and current drug use, physical examination with special attention for the heart and lungs, blood pressure, heart rate, blood tests, ECG, and any other diagnostic procedures the physician considers necessary. The standard blood tests include measurements of troponin, glucose levels, creatinin levels (with a calculated estimated glomerular filtration rate (eGFR) according to MDRD (modification of diet in renal disease)), haemoglobin, and any other blood test required. A standard 12-lead ECG is recorded by a trained employee of the ED and classified by a single cardiologist according to the Minnesota coding criteria. All investigations take place in the ED.

During the HEART period, the HEART score will be formally determined in all patients. Decision-making about whether to admit a patient, any further testing or treatment decisions will be carried out similarly to usual care, with the exception of the availability of the HEART score in each individual patient and the recommendations linked to that score. This is also known as “directive use” of a prediction rule, as opposed to “assistive use” where only the predicted risk is given to the physician [19]. The recommendation for patients with a HEART score of 3 or lower will be reassurance and discharge. In those low-risk patients who are discharged, a second troponin will be performed at home to identify any missed ACS. A similar approach of home visits performed by ambulatory lab services was successfully applied in our earlier study in suspected ACS in primary care [20]. Obviously, in accordance with daily practice, the attending physician may decide to overrule the recommendation corresponding to a low HEART score and admit a patient. In such a case, information about the reasoning for this escape will be collected. Patients with a HEART score in the intermediate range (4–6), will generally be admitted to the hospital for further observation and investigation. The high-risk group (7–10) will typically receive prompt (invasive) treatments.

### Study population and recruitment

All patients above 18 years presenting with chest pain to the (cardiac) ED of 10 participating hospitals are eligible. Only patients presenting with evident ST-segment elevation myocardial infarction (STEMI) will be excluded, since there is no diagnostic dilemma in these patients. Typically, such patients are directly taken to the intervention room. In both study periods, information about the study procedure will be provided by the treating physician and written consent for the use of data and follow-up is obtained at the first appropriate moment after presentation at the ED. In the HEART period, no consent from the patient is needed for the use of the HEART score, for several reasons. First, the number of additional procedures for patients is minimal since the HEART score consists of elements that are collected routinely. Furthermore, the HEART score is proven to be safe, and is a decision support tool rather than a real intervention, with the possibility for physicians to override the recommendations provided by the rule. The study was approved by the Institutional Review Board, and subsequently by the Boards of the participating hospitals.

### Outcome measures

The HEART impact trial aims to measure both the intended positive changes as well as any unintended negative effects associated with the use of the HEART score. Patient outcomes, use of health care resources and costs will be determined in both periods.

#### Primary outcome: occurrence of MACE

The primary outcome is the 6-week occurrence of major adverse cardiac events (MACE), consisting of the following events: acute myocardial infarction (AMI), Percutaneous Coronary Intervention (PCI), Coronary Artery Bypass Grafting (CABG) surgery, or death due to any cause. To identify MACE after discharge, a phone-call will be made to all patients at home after 3 months. Any information that could indicate to possible endpoints will be further investigated through hospital charts, hospital discharge letters and information obtained from the patient’s general practitioner (GP). In addition, the Central Bureau for Statistics (CBS) will be consulted for information on vital status as the cause of death of participants. All cases with possible endpoints are reviewed by two independent adjudicators for endpoint classification. This adjudication committee will evaluate all relevant information to decide, using ESC guidelines, whether MACE occurred. In case of disagreement between two adjudicators, the case is discussed in a plenary adjudication committee meeting until consensus is reached.

Secondary outcomes include the following:

•The occurrence of MACE in the specific subgroup of patients with a low HEART score.

•Use of health care resources. The number of hospital admissions/discharges, duration of hospital stay, duration of stay on the ED, number of readmissions and GP visits after discharge will be collected.

•Health-related quality of life. This will be determined in a subset of approximately 1000 patients, in both time periods in five of the participating hospitals. Data on health-related quality of life are collected at baseline (at ED) using the EuroQol Five-Dimensional (EQ-5D) questionnaire, and a 2-week and at 3-month follow-up using the short form-36 (SF-36) and the EQ-5D questionnaires. SF-36 is a short-form health survey with only 36 questions. For this study, we will only use the 11 questions addressing Health. EQ-5D comprises the following 5 dimensions: mobility, self-care, usual activities, pain/discomfort and anxiety/depression. Furthermore, the EQ VAS (visual analogue scale) records the respondent’s self-rated health on a vertical, visual analogue scale where the endpoints are labelled ‘Best imaginable health state’ and ‘Worst imaginable health state’. Higher scores are associated with a better health-related quality of life.

•Direct and indirect costs. These will be determined in a subset of approximately 1000 patients, in both time periods in five of the participating hospitals*.* Actual medical costs using a health-care provider’s perspective are obtained in both the time periods. Medical resource use is extracted from the electronic hospital patient files. Unit cost prices will be determined in two participating hospitals, one academic and one peripheral hospital, using micro-costing if possible and top down costing otherwise. The iPCQ (Productivity Cost Questionnaire) will be used to collect quantitative data on the relation between illness, treatment and work performance. The iPCQ is divided into 3 modules: (1) reduced productivity at paid work due to work absenteeism, (2) reduced productivity at paid work without absence from work and (3) unpaid labour production.

•An additional sample of blood will be collected from patients of two participating hospitals during the emergency visit for future biomarkers investigation (Biobanking).

### Statistical analyses

The 6-week cumulative incidence of MACE in both the intervention and usual care period will be analysed at the patient level using a generalised linear mixed model (GLMM) [21]. Risk differences with corresponding 95% CIs will be estimated from this model. No baseline differences in prognostic factors between patients included in both periods are expected, but in case these do occur, covariates will be added to the GLMM model to adjust for these baseline differences. Differences in health-related quality of life at baseline, 2 weeks and at 3 months will also be assessed, separately for the different questionnaires. Costs per patient will be calculated according to Dutch guidelines for pharmaco-economic analyses [22], and costs of drugs prescribed will be based on Dutch formulary cost-prices.

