### Sample size

The aim of the HEART study is to evaluate whether the use of the HEART score streamlines the further management of chest pain patients, in particular whether it can identify low-risk patients who can be discharged sooner than usual. However, these benefits become only relevant if the use of the HEART score does not lead to an increase in adverse cardiac events. Our sample size calculation is therefore based on demonstrating that proportion of patients with MACE is not inferior to the proportion observed with usual care. The proportion MACE expected during usual care is 17%. The non-inferiority margin is based on clinical judgement and available literature as 3%, thus accepting an upper limit of the 95% confidence interval (CI) during the intervention period of 20%. With 10 hospitals, inclusion of 60 patients per hospital per month, a between-hospital variation in incidence of 16 to 18%, a one-sided alpha of 5% and a power of 80%, 6600 patients with chest pain should be included in total. Taken into account our inclusion rates of previous validation studies and with special attention and encouragement for inclusion, we expect a realistic inclusion rate of 60 patients per hospital per month.

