### Cost-effectiveness analysis

A cost-effectiveness analysis will be performed from a societal perspective, for a 3-month and a life-time time horizon. The 3-month time horizon corresponds to the actual follow-up period and will consider the observed differences in costs and quality of life. A GLMM will be used to assess cost-effectiveness, accounting for the randomisation of clusters instead of patients. Uncertainty will be addressed through the GLMM model which will be extended with cluster and patient-level covariates if baseline characteristics are imbalanced. The life-time horizon will be applied to account for long-term costs and effects of the observed MACE. Here, the observed risks of MACE, as well as the direct treatment cost and productivity losses estimated using the friction cost approach, will serve as input for a Markov decision-analytic model [23]. If necessary, additional evidence on long-term costs and effects of adverse events will be obtained from the literature. Monte Carlo simulation will be applied to simulate the course of hypothetical patients through the model, and to estimate the number of quality-adjusted life years and costs of both strategies. Costs will be discounted with 4% per annum, and effects with 1.5% per annum, according to Dutch guidelines. The incremental cost-effectiveness ratio and the net monetary benefit (for various willingness to pay thresholds) will be estimated for the HEART score compared with usual care. Uncertainty will be assessed with probabilistic sensitivity analysis [24], and results will be presented in incremental cost-effectiveness planes and cost-effectiveness acceptability curves.

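### Covariates enter the primary model only if baseline imbalance is seen; a short fixed set would remove a data-driven choice and usually recover some precision

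*Protocol article*

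**What the plan says.** The Statistical analyses section plans a patient-level GLMM for the 6-week incidence of MACE and states that "Risk differences with corresponding 95% CIs will be estimated from this model". It then says that no baseline differences in prognostic factors are expected between the periods, but "in case these do occur, covariates will be added to the GLMM model to adjust for these baseline differences". It does not say what counts as a difference or which covariates are candidates.

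The Cost-effectiveness analysis section repeats the rule: that model will be "extended with cluster and patient-level covariates if baseline characteristics are imbalanced".

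Two other sections bear on the point:

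- On data available before the switch, the section on the usual care and HEART periods says "The assessment will typically include: gender, age, medical (cardiac) history, symptoms, risk factors, and current drug use". It also lists troponin as a standard blood test and has the ECG classified by a single cardiologist to the Minnesota criteria.
- On inclusion, Study population and recruitment says that "written consent for the use of data and follow-up is obtained at the first appropriate moment after presentation at the ED".

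**The concern.** The primary question is whether MACE under the HEART score is non-inferior to usual care within 3 percentage points. Under the stated rule, whether the deciding estimate is adjusted, and for what, depends on the observed imbalance. Without a criterion or a list, several models remain open once the data are known, and a safety conclusion should not rest on that choice.

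The rule also treats adjustment only as a repair for imbalance. Adjusting for strong predictors narrows the confidence interval of a risk difference even when the groups are balanced, and the protocol's own Table 2 shows how strongly baseline findings separate MACE risk.

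The expectation of balance is optimistic for this design. Ten hospitals are randomised only to their switch time, patients are not randomised, and consent is sought when the hospital's current period is already known.

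**Working it through.** **Inputs from the protocol.** Sample size section: usual-care MACE 17%, margin 3 points, 10 hospitals, 60 patients per hospital per month, one-sided alpha 5%, power 80%, N = 6600, between-hospital incidence 16 to 18%. Study design section: 11 months, one hospital switching each month after the first. Table 2: MACE by HEART category. The between-hospital SD is not given. I use 0.005 (16–18% read as ±2 SD) and 0.010 (read as ±1 SD).

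**Step 1. Reproduce the planned power.** Stepped-wedge variance (Hussey–Hughes) with random hospital intercepts and fixed month effects:

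Var = I·s·(s + T·τ²) / [(I·U − W)·s + (U² + I·T·U − T·W − I·V)·τ²]

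- I = 10, T = 11, s = 0.17 × 0.83 / 60 = 0.002352.
- U = 55 hospital-months under HEART. W = V = 1² + … + 10² = 385.
- I·U − W = 550 − 385 = 165. U² + I·T·U − T·W − I·V = 3025 + 6050 − 4235 − 3850 = 990.
- τ = 0.005: Var = 10 × 0.002352 × 0.002627 / (0.3880 + 0.0248) = 0.0001497, so SE = 0.01223. Power = Φ(0.03/0.01223 − 1.645) = Φ(0.807) = 0.790.
- τ = 0.010: SE = 0.01291, power 0.751.

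The first reading reproduces the stated 80% closely.

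**Step 2. How much MACE variance does baseline risk explain?** Table 2 prints no category shares, but they follow from its pooled confidence intervals through n = 1.96²·p(1 − p)/h², where h is the half-width:

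- Score 0–3: p = 0.016, h = 0.0055, n ≈ 1,999.
- Score 4–6: p = 0.125, h = 0.0116, n ≈ 3,123.
- Score 7–10: p = 0.494, h = 0.0303, n ≈ 1,046.

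The sum is 6,168, against 6,174 stated, giving shares of 0.324, 0.506 and 0.170. Then R² = Σw(p − p̄)² / [p̄(1 − p̄)]:

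- Pooled rates: p̄ = 0.152, R² = 0.0262 / 0.1291 = 0.203.
- Dutch multicentre rates (1.7, 16.6, 50.1%) on the same shares: p̄ = 0.175, R² = 0.0262 / 0.1441 = 0.182.
- Dutch rates with the low-risk share assumed at 20 to 50%, the rest solved to give 17% overall: R² = 0.112 to 0.265.

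These values are for the full HEART category. Age, sex, troponin and ECG alone would capture only part of it, so I assume that they remove 5 to 15% of residual variance.

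**Step 3. Effect on power.** Repeat step 1 with s multiplied by (1 − R²), at one-sided 5%:

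| Residual variance removed | τ = 0.005: SE, power | τ = 0.010: SE, power |
|---|---|---|
| 0 | 0.01223, 0.790 | 0.01291, 0.751 |
| 5% | 0.01194, 0.807 | 0.01262, 0.768 |
| 10% | 0.01163, 0.825 | 0.01232, 0.785 |
| 15% | 0.01132, 0.843 | 0.01202, 0.803 |

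**Step 4. How would an imbalance trigger behave?** A simulation used 4,000 trials per scenario, a linear model with hospital and month fixed effects, hospital SD 0.010 and a low-risk share of 36%. It supposed a trigger of p < 0.05, since the protocol states none.

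- With no true imbalance, the trigger fired in about 5% of trials.
- Empirical SE was 0.0163 unadjusted, 0.0161 triggered and 0.0145 always adjusted. Power was 0.58, 0.58 and 0.67. The ratio (0.0145/0.0163)² = 0.79 corresponds to about 21% of variance removed, so the always-adjusted figure reflects information worth the full HEART category and is an upper guide. Absolute power is lower than in step 1 because fixed hospital effects use only within-hospital information.
- With a true difference equal to the margin, the rate of false non-inferiority claims was 0.046 unadjusted and 0.046 triggered. It was 0.070 if whichever of the adjusted and unadjusted results passed could be used.

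**The case against.** The planned rule already adjusts when recorded prognostic factors differ, so fixed adjustment adds little protection against measured imbalance. That is right. What remains is the open choice of model and the precision.

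An article may leave the criterion and the list to an analysis plan that is not shown. That also stands for those details. It does not cover the rule itself, which the article states: a plan that implemented it faithfully would still choose the primary model from the observed data.

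A reader might infer more than the document supports:

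- That the expectation of balance is wrong. Patients are unselected apart from evident STEMI, consent is sought in both periods, and Table 3 notes that within-hospital comparison may be less confounded by case mix. Differential inclusion is a plausible risk that the document does not demonstrate.
- That the rule inflates type I error. A fixed trigger did not (0.046). The 0.070 needs freedom to claim success on either result, which the protocol does not grant but also does not explicitly close off.
- That the trial is underpowered without adjustment. At its stated one-sided 5% it reaches about 79% on the first SD reading, essentially its target. Whether the 95% confidence interval implies one-sided 2.5% is a separate question and is not part of this gain.
- That every HEART component should be adjusted for. Usual care is explicitly not standardised, and risk factors are only typically assessed there, whereas the score is formally determined in all patients in the HEART period. Risk-factor count and atherosclerotic history may therefore be recorded more completely after the switch, and adjusting for them could introduce bias. The same holds for the HEART total and its History item.

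**Conclusion.** The point holds as a worthwhile, low-cost improvement. The protocol ties the primary model to observed imbalance without a criterion or list, which makes the non-inferiority estimate depend on a data-driven choice and, under a conventional trigger with balanced groups, almost always forgoes the available precision.

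The expected gain is about 2 to 5 percentage points of power: 79% to 81–84% (hospital SD 0.005) or 75% to 77–80% (SD 0.010).

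This rests on several assumptions. The 5 to 15% reduction is assumed, on a linear-scale R². The Table 2 studies define MACE differently, and the pooled high-category rate of 49.4% lies below all three study values (65.2, 50.1, 50.0%), so R² is indicative only. The gain applies to the risk difference, which is the stated measure; the SE of a conditional log odds ratio would not shrink in this way. Adjustment cannot address imbalance in factors that are not measured.

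**What to change.** Replace the conditional clause in the Statistical analyses section with a fixed rule, set before any outcome comparison:

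- The primary GLMM always includes age, sex, presenting troponin category and Minnesota-coded ECG class, in addition to its design terms. Confirm that the ECG is coded by the same process in both periods.
- The risk difference is obtained by standardising over the study population, with a named confidence interval method that respects clustering by 10 hospitals.
- Atherosclerotic history or risk-factor count is added only if the same standard form records it in both periods. The physician's HEART total is not used.
- The estimate without patient covariates is reported as supportive, and the text says that it cannot replace the primary result.

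Make the same change in the Cost-effectiveness analysis section.

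The cost is plan wording, a stated method for missing covariate values, and programming of the standardisation and its interval, which needs some care with 10 clusters. The items belong to the routine assessment, so no extra patients or visits are needed.

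### Baseline EQ-5D appears only as a time point to compare between periods; it should be prespecified as a covariate for the 2-week and 3-month quality-of-life comparisons and the 3-month cost-effectiveness model

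*Protocol article*

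**What the plan says.** All places are in the protocol article, under Methods/Design.

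- **Statistical analyses**, on quality of life: "Differences in health-related quality of life at baseline, 2 weeks and at 3 months will also be assessed, separately for the different questionnaires". The sentence names no model and no covariate.
- **Outcome measures**, list of secondary outcomes. At baseline: "Data on health-related quality of life are collected at baseline (at ED) using the EuroQol Five-Dimensional (EQ-5D) questionnaire". Afterwards: "and a 2-week and at 3-month follow-up using the short form-36 (SF-36) and the EQ-5D questionnaires". EQ-5D is therefore measured three times and SF-36 twice. On the sample: "This will be determined in a subset of approximately 1000 patients, in both time periods in five of the participating hospitals".
- **Statistical analyses**, on baseline differences in prognostic factors, within the account of the MACE model: "in case these do occur, covariates will be added to the GLMM model to adjust for these baseline differences".
- **Cost-effectiveness analysis**: the 3-month horizon "will consider the observed differences in costs and quality of life", and uncertainty is handled through a "GLMM model which will be extended with cluster and patient-level covariates if baseline characteristics are imbalanced".

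**The concern.** A difference in baseline quality of life between the two periods does not measure what the HEART score does to later quality of life. In the effect analysis, the baseline score is useful as a covariate: it explains part of the spread in the follow-up scores and corrects for patients who entered the two periods in different health. The article lists it alongside the follow-up points and gives it no such role.

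Imbalance is plausible here. Patients are not randomised individually. Consent is obtained after presentation, when the hospital's current period is already in force. HEART-period patients present later in calendar time on average. Only five of the ten hospitals contribute, so the balance expected from ten randomised switch dates is only partly available.

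A rule triggered by observed imbalance is a weak remedy. It forgoes the precision gain whenever no imbalance is seen, and it leaves the choice of model open until the data are known. At stake are the precision of a secondary outcome, its protection against chance and calendar differences, and the EQ-5D input to the 3-month cost-effectiveness result.

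**Working it through.** **No stated figure to reproduce.** The article gives no power, standard deviation, effect size or correlation for quality of life, only a subset of about 1000. The total of 6600 (10 hospitals × 60 patients × 11 months) was set for MACE non-inferiority and does not bear on this point.

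**What each provision covers.**

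| Analysis | Adjustment stated | Condition |
|---|---|---|
| MACE GLMM | covariates, not named | only if baseline differences occur |
| Quality of life at 2 weeks and 3 months | none stated | – |
| Cost-effectiveness GLMM | cluster and patient-level covariates, not named | only if characteristics are imbalanced |

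Baseline EQ-5D is named in none of the three rows.

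**Questionnaires by time point.** EQ-5D: baseline, 2 weeks, 3 months. SF-36: 2 weeks, 3 months. The analysis sentence lists baseline for the questionnaires collectively, but only EQ-5D has a baseline value.

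**Size of the possible gain.** Assumptions, none taken from the article: baseline-to-follow-up correlation r between 0.3 and 0.6; 1000 patients split 500/500; independent patients; no period effects.

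- Residual variance factor after adjustment: 1 − r².
- Equivalent number of patients: 1000 / (1 − r²).
- Detectable difference in SD units (80% power, two-sided 5%): (1.960 + 0.842) × √(4(1 − r²)/1000).

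| r | 1 − r² | Variance removed | Equivalent N | Detectable difference |
|---|---|---|---|---|
| 0 (unadjusted) | 1.00 | 0% | 1000 | 0.177 SD |
| 0.3 | 0.91 | 9% | about 1099 | 0.169 SD |
| 0.5 | 0.75 | 25% | about 1333 | 0.153 SD |
| 0.6 | 0.64 | 36% | about 1563 | 0.142 SD |

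**Imbalance carried forward.** If mean baseline scores differ by b SD between periods, and the SD is the same at baseline and follow-up, an unadjusted follow-up comparison carries about r × b. For an assumed b of 0.1 SD this is 0.3 × 0.1 = 0.03 SD up to 0.6 × 0.1 = 0.06 SD.

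**Limits.** The formulas ignore hospital clustering and the information lost to estimating calendar-time effects in five hospitals, so the equivalent numbers of patients do not transfer directly to this design. They also apply to EQ-5D adjusted for its own baseline. The gain for SF-36 from a different instrument's baseline is not quantified.

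**The case against.** The strongest reply is that the article does not rule out baseline adjustment, and that models and covariates for a secondary outcome are commonly left to the full protocol or SAP, which is not shown. This stands against several stronger readings that a reader might infer:

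- *Each time point is analysed separately.* The word in the analysis sentence separates the questionnaires, not the time points. A joint longitudinal model remains open.
- *Baseline EQ-5D is excluded as a covariate.* The article does not say so; this would be an inference from silence.
- *Period differences are left uncorrected.* This disregards the conditional rule in the Cost-effectiveness analysis section, which covers a model that uses quality of life.
- *The SF-36 analysis cannot be done.* SF-36 can be compared at both follow-ups. Only its baseline comparison is impossible, which is a wording mismatch between two sections.

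Two further objections have force. Without individual randomisation and with consent after presentation, a look at baseline quality of life helps show whether the consented patients differ between periods, so it should be kept as description. Also, the article does not say that the emergency-department questionnaire is completed before the HEART-based advice is given. If it can come afterwards, the baseline EQ-5D, which includes anxiety/depression, could already reflect the intervention, and adjusting for it could absorb part of the effect.

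The reply does not remove the point. The article does state a role for baseline, as a comparison, and it does state adjustment rules, all of them conditional on observed imbalance.

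**Conclusion.** The point holds in a limited form. The article gives baseline quality of life a role as a between-period comparison and none in the follow-up comparisons, and the only adjustment it describes depends on observed imbalance. Prespecifying the baseline EQ-5D already planned for collection would improve the quality-of-life and 3-month cost-effectiveness analyses at almost no cost.

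For independent patients the gain is 9% to 36% less residual variance at r = 0.3 to 0.6. Its true size cannot be fixed from the article, because r is unstated and clustering and period effects are ignored. Confidence is moderate, mainly because the timing of the baseline questionnaire is not given. This is a recommended improvement to a secondary outcome. If an SAP already prespecifies the adjustment, only the wording on SF-36 remains.

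**What to change.** 1. Prespecify baseline EQ-5D as a covariate, regardless of observed imbalance, in mixed models with hospital and calendar month for EQ-5D and SF-36 at 2 weeks and 3 months.
2. Include the same covariate in the 3-month cost-effectiveness GLMM.
3. Keep the baseline comparison between periods, labelled as descriptive.
4. State that baseline applies to EQ-5D only, so that the Statistical analyses section agrees with the list of secondary outcomes.
5. Confirm whether the emergency-department questionnaire is completed before the HEART-based advice is given, and report an unadjusted sensitivity analysis.

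The cost is wording in the SAP, one check of data-collection procedure and one extra model run per outcome. No new data are needed. The small downside is the possible loss of part of the effect if the questionnaire follows the advice; step 5 is there to expose it.
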